## 2.4 Secondary Endpoint

1. Clinical status assessed by the seven-category ordinal scale.
2. The requirement of ICU admission or Mechanical ventilation
3. 28- and 90-days mortality.
4. PCR test negative conversion rate and days from positive to negative\*\*
5. Evaluate the safety of investigational therapeutics as compared to the control arm.
6. Length of hospital stay.
7. Duration of fever.
8. QT prolongation (Daily follow up during the concomitant use of both medications and regularly till Day14)

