### 7.3 Safety monitoring

Site PI should follow on a daily basis all the possible AEs while using the investigational medications and up to day-14. This includes regular monitoring of hematology and blood chemistry. Daily ECG and QT interval monitoring. And LFT every other day. In case of any concerns that might require holding/stopping medication, causality assessment should be done by PI and with a consultation to an independent clinician.

Details of cardiac toxicity monitoring as follow:

1. A baseline ECG before starting then daily ECG after.
2. Daily ECG to be done through day 1-10 or twice daily if the corrected QT interval more than 480ms.
2. Maintain serum level of Mg>1.0 meq, and K>4.5 meq throughout the 10 days of therapy.
3. If the QTc prolonged more than 500ms after starting, stop the medication.
4. Avoid any other QT prolong medication during the regimen.
5. If the patient develops torsades de-pointes, stop the medication immediately, follow ACLS protocol and call the cardiologist on-call.

If you have any query or help, please call for cardiology team in you center.

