#### 7.4 Follow-up Period

The follow up period would be till discharge from the hospital or day 28 from randomization.

Where serial oropharyngeal swab or lower respiratory samples will be obtained on day 1 (-3 days) (before therapy was administered) and on days  $5 \pm 1$  day,  $10 \pm 2$  days,  $14 \pm 2$  days,  $21 \pm 2$  days, and  $28 \pm 3$  days or until 2 consecutive testing are negative which comes first. Any extra Respiratory PCR COVID19 samples requested by the treating team will be recorded. Other laboratory investigations will be recorded as per flow chart.

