## 8. FLOW CHART

Table 4: Flow Chart

|                                                 | Study period |                 |    |     |    |     |    |     |     |     |     |          |
|-------------------------------------------------|--------------|-----------------|----|-----|----|-----|----|-----|-----|-----|-----|----------|
|                                                 | Baseline     | Post allocation |    |     |    |     |    |     |     |     |     | Closeout |
| Timepoint study days                            | D0           | D1              | D2 | D'' | D5 | D'' | D9 | D10 | D'' | D14 | D21 | D28      |
| Enrolment and assignment                 |              |                 |    |     |    |     |    |     |     |     |     |          |
| Eligibility assessment                          | X            | X               |    |     |    |     |    |     |     |     |     |          |
| Informed consent                                | X            | X               |    |     |    |     |    |     |     |     |     |          |
| Randomization                                   | X            | X               |    |     |    |     |    |     |     |     |     |          |
| Baseline data                                   | X            | X               |    |     |    |     |    |     |     |     |     |          |
| Study drug administration                |              |                 |    |     |    |     |    |     |     |     |     |          |
| Favipiravir                                     |              | X               | X  | X   | X  | X   | X  | X   |     |     |     |          |
| Hydroxychloroquine                              |              | X               | X  | X   | X  |     |    |     |     |     |     |          |
| Adverse effect reaction                         |              | X               | X  | X   | X  | X   | X  | X   | X   | X   |     |          |
| Serious adverse event assessment                |              | X               | X  | X   | X  | X   | X  | X   | X   | X   | X   | X        |
| Clinical data collection                 |              |                 |    |     |    |     |    |     |     |     |     |          |
| Seven-category ordinal scale and CRF            | X            | X               | X  | X   | X  | X   | X  | X   | X   | X   | X   | X        |

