| Laboratory data collection               |              |                 |    |     |    |     |    |     |     |     |     |          |
| Covid-19 PCR from Respiratory sample *          | X            | X               |    |     | X  |     |    | X   |     | X   | X   | X        |
| CBC, renal profile and LFT on Study Drug | X            | X               | X  | X   | X  | X   | X  | X   |     | X   | X   |          |
| CBC, renal profile and LFT on SoC        | X            | X               |    |     | X  |     |    | X   |     |     | X   |          |

|                                             |   |   |   |   |   |  |  |   |  |  |  |  |
|---------------------------------------------|---|---|---|---|---|--|--|---|--|--|--|--|
| ECG for patient on Study Drug | X | X | X | X | X |  |  | X |  |  |  |  |
| ECG for patient on SoC        | X | X |   |   | X |  |  | X |  |  |  |  |

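### Safety monitoring (7.3) requires a daily ECG on days 1–10 of study drug, but the flow chart (Table 4) schedules none on days 6–9

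*Protocol*

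**What the plan says.** Section 7.3 (Safety monitoring) asks for a baseline ECG and daily ECGs afterwards, then gives the range and the escalation: "Daily ECG to be done through day 1-10 or twice daily if the corrected QT interval more than 480ms". Two further items depend on monitoring through the whole course: "Maintain serum level of Mg>1.0 meq, and K>4.5 meq throughout the 10 days of therapy" and "If the QTc prolonged more than 500ms after starting, stop the medication".

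Section 7.2 (Treatment Period) gives favipiravir for 10 days and hydroxychloroquine for 5.

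In Section 8, the Table 4 row labelled "ECG for patient on" study drug has marks at D0, D1, D2, the first D'' column, D5 and D10, and nowhere else. In the block headed "Study drug administration", the favipiravir row is marked in every column from D1 to D10. The study-drug row labelled "CBC, renal profile and LFT on" is marked in every column from D0 to D10, and again at D14 and D21.

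The QT item among the secondary endpoints (2.4) reads "QT prolongation (Daily follow up during the concomitant use of both medications and regularly till Day14".

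**The concern.** Two parts of the same protocol give different ECG schedules for treated patients, and nothing says which governs. Flow charts are commonly what sites use to book procedures. Both rules in 7.3, twice-daily ECGs above 480 ms and stopping above 500 ms, work only if an ECG is taken.

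A site that books from Table 4 could leave a patient with QTc of 481–500 ms on day 5 without a tracing until day 10, when 7.3 wants two a day. The toxicity appendix grades an average QTc of 501 ms or more as Grade 3, and Section 9.4 compares Grade 3 or higher events between arms. Missed ECGs could therefore also reduce detection of a compared safety outcome, and unevenly if sites follow different sources.

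**Working it through.** No sample size, power or alpha figure is involved. The check matches the 12 cells of each Table 4 row to its 12 day columns: D0, D1, D2, D'', D5, D'', D9, D10, D'', D14, D21, D28. The D'' columns are read as the days between their neighbours: 3–4, 6–8 and 11–13. The drug rows support this reading, because it gives hydroxychloroquine days 1–5 and favipiravir days 1–10, as in 7.2.

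| Days | ECG on study drug, 7.3 | ECG on study drug, Table 4 | Favipiravir, Table 4 | Hydroxychloroquine, Table 4 | Study-drug bloods, Table 4 |
|---|---|---|---|---|---|
| 1–5 | daily | marked | marked | marked | marked |
| 6–8 | daily | blank | marked | blank | marked |
| 9 | daily | blank | marked | blank | marked |
| 10 | daily | marked | marked | blank | marked |
| 11–13 | beyond the stated day range | blank | blank | blank | blank |
| 14 | beyond the stated day range | blank | blank | blank | marked |

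- **Days 1–10:** 7.3 requires 10 ECG days. Table 4 schedules days 1, 2, 3, 4, 5 and 10, which is 6. The gap is 10 − 6 = 4 days (6, 7, 8 and 9).
- **Favipiravir-only days:** these are days 6–10, so 10 − 5 = 5. Table 4 has an ECG on 1 of them and 7.3 on all 5.
- **Above 480 ms:** if QTc stays in that range, 7.3 calls for 2 × 4 = 8 tracings on days 6–9. Table 4 has none.
- **Early discharge:** the Protocol Summary ends favipiravir at discharge if that comes before day 10. If the last favipiravir day is L, the gap is 0 for L ≤ 5, L − 5 for L from 6 to 9 (1 to 4 days), and 4 for L = 10. Four is the maximum per patient.
- **After day 10:** Table 4 has no ECG on days 11–14.

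A shifted row in the extracted table is an unlikely cause. The row has exactly 12 cells. The standard-of-care ECG row beneath it falls on D0, D1, D5 and D10, the same columns as the standard-of-care blood row through D10.

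**The case against.** The best defence is that 7.3 is the specific cardiac instruction, with a day range, thresholds and a stopping rule. The ECG rows sit in the laboratory block of Table 4, and 7.4 says of that material: "Other laboratory investigations will be recorded as per flow chart". On this view the table is a minimum collection schedule and does not cancel 7.3. This makes a missed ECG conditional on how a site reads the protocol. It does not remove the contradiction, because no precedence is stated and the blood row beside it is marked on the very days the ECG row is blank.

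A second defence is that ECGs were meant to thin out once hydroxychloroquine ended. The text of 7.3 does not allow that: it names days 1–10 and keeps magnesium and potassium controlled for all 10 days.

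Some stronger readings are tempting but are not supported:

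- A reader might infer that QT findings on days 6–9 would have nowhere to be recorded. The opening of Section 7 requires all assessments to be documented in the eCRF, 7.1 requires daily reporting, and the adverse-effect row of Table 4 is marked from D1 to D14.
- A reader might infer that days 6–9 breach a daily requirement in the QT endpoint. Section 2.4 asks for daily follow-up only while both drugs are given (days 1–5), and Table 4 covers that in full. The day 6–9 conflict is with 7.3.
- A reader might infer that ECGs are absent from day 10 onwards. D10 is marked; the absence starts at day 11.
- A reader might infer that the day-14 mismatch lies with 2.4 alone. The opening of 7.3 follows adverse events to day 14 and mentions daily ECG and QT monitoring in the same paragraph, and its first numbered item has no end date. That section can also be read as reaching day 14.

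**Conclusion.** The inconsistency is real and should be corrected. Table 4 omits up to 4 of the 10 ECG days that 7.3 requires, all while favipiravir is being given. This rests on reading the D'' columns as the intervening days and on the patient still being on favipiravir through day 9.

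The consequence is limited. Section 10.2 lists QTc prolongation for hydroxychloroquine and not for favipiravir, and hydroxychloroquine stops on day 5. Days 1–5 are covered daily. The primary analysis, power and alpha are not affected.

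The lack of an ECG on days 11–14 is a secondary remark. Section 2.4 calls for QT follow-up to day 14 but sets no frequency, so the documents do not fix which day or days should be marked.

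**What to change.** In the study-drug ECG row of Table 4, mark the second D'' column (days 6–8) and D9. These two cells add no procedure beyond what 7.3 already requires, and study-drug bloods are scheduled on the same days. In the table, ECG days within days 1–10 go from 6 on study drug against 3 on standard of care (D1, D5, D10) to 10 against 3. That difference already follows from 7.3.

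For the period after day 10, choose one of two options:

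- State the last QT time point identically in 2.4, the Protocol Summary, 7.3 and Table 4. This is a wording change only.
- Add a D14 ECG for patients still in hospital, in both ECG rows. This is a new procedure of one ECG per such patient. Adding it in the treated arm alone would widen the difference in ECG ascertainment between arms.

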#### 7.4 Follow-up Period

The follow up period would be till discharge from the hospital or day 28 from randomization.

Where serial oropharyngeal swab or lower respiratory samples will be obtained on day 1 (-3 days) (before therapy was administered) and on days  $5 \pm 1$  day,  $10 \pm 2$  days,  $14 \pm 2$  days,  $21 \pm 2$  days, and  $28 \pm 3$  days or until 2 consecutive testing are negative which comes first. Any extra Respiratory PCR COVID19 samples requested by the treating team will be recorded. Other laboratory investigations will be recorded as per flow chart.

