## 2. STUDY OBJECTIVES AND ENDPOINTS

### 2.1 Primary Objectives

The improvement of two points (from the status at randomization) on a seven-category ordinal scale\* or live discharge from the hospital, whichever came first.

\*The seven-category ordinal scale consists of the following categories:

8. Not hospitalized with resumption of normal activities
9. Not hospitalized, but unable to resume normal activities
10. Hospitalization, not requiring supplemental oxygen
11. Hospitalization, requiring supplemental oxygen
12. Hospitalization, requiring nasal high-flow oxygen therapy and/or non-invasive mechanical ventilation
13. Hospitalization, requiring ECMO and/or invasive mechanical ventilation
14. Death.

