#### 10.4 Handling of Serious Adverse Events

All adverse drug events encountered during the clinical study will be reported on the CRF. Serious adverse events (SAEs), whether or not associated with study medication administration, will be recorded both on the Adverse Event form of the CRF as for non-serious AE and the SAE form.

ALL SAEs occurring during this study and up to 30 days after a subject discontinued or completed the study, whether or not related to the administration of study medication, must be reported by faxing the completed SAE form, after reviewing the report for consistency and accuracy within 24 hours of awareness by the investigator, to KAIMRC / IRB.

As far as possible, investigators should follow-up participants with AEs until the event is resolved or until, in the opinion of the investigator, the event is stabilized or determined to be chronic. Details of AE resolution must be documented in the CRF. Participants should be followed-up for 30 days after receiving the last dose of study medication and any AEs, which occur during this time, should be reported according to the procedures outlined above. Any significant changes in AEs should be reported even though the subject has completed the study, including the protocol-required post-treatment follow-up.

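### 90-day mortality is a listed secondary endpoint but nothing in the Protocol collects it, and section 7.4 conflicts with the flow chart on follow-up after discharge

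*Protocol*

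**What the plan says.** Protocol section 2.4, repeated in the Summary, names "28- and 90-days mortality" among the secondary endpoints. Clinical status on the seven-category scale is the first item on the same list.

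Section 7.4 fixes the length of follow-up: "The follow up period would be till discharge from the hospital or day 28 from randomization". It does not say whether the earlier or the later of the two applies.

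The flow chart (section 8, Table 4) has a row headed "Timepoint study days" that runs from D0 to D28, and the D28 column is labelled as closeout. The rows "Seven-category ordinal scale and CRF" and "Serious adverse event assessment" are both marked up to D28, with no exception for patients who have gone home. The scale has death as one category and two categories for people outside hospital, one of them "Not hospitalized, but unable to resume normal activities" (section 2.1).

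Section 10.4 sets two further windows. Reporting covers "ALL SAEs occurring during this study and up to 30 days after a subject discontinued or completed the study". It also says: "Participants should be followed-up for 30 days after receiving the last dose of study medication". Section 10.1 counts death as an SAE.

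**The concern.** An endpoint can be reported only if some procedure collects it. For day 90 the Protocol names the endpoint and provides no contact. An analysis plan cannot repair this, because it cannot create data that the sites were never asked to collect. At database lock the sponsor would have to drop the endpoint, or report something narrower, such as in-hospital mortality, under the 90-day label.

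For day 28 the problem is different. Section 7.4 and the flow chart give sites two instructions for a discharged patient. A site that stops at discharge can point to 7.4, and a site that continues to D28 can point to Table 4. At stake are the post-discharge scores for the first secondary endpoint, and a confirmed day-28 vital status rather than one inferred from the absence of a report.

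**Working it through.** **1. Does any window reach day 90?**

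| Source | Latest day covered | Gap to day 90 |
|---|---|---|
| Section 7.4, follow-up | 28 | 90 − 28 = 62 days |
| Section 8, flow chart | 28 | 62 days |
| Section 10.4, SAE reporting after completion | 28 + 30 = 58 | 90 − 58 = 32 days |
| Section 10.4, 30 days after last dose, 10-day course | 10 + 30 = 40 | 90 − 40 = 50 days |

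No window reaches day 90. The shortfall is at least 32 days for every patient, discharged or not. Only patients already known to have died have a known day-90 status.

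**2. Is there calendar room?** The Summary and section 14 put the last patient's first visit in May 2021 and the last visit in November 2021, about six months later. A 90-day check fits.

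**3. Is day 28 covered for a discharged patient?**

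- Section 7.4 read alone, taking the earlier of the two dates: no.
- Flow chart: yes. The ordinal scale and SAE assessment are marked at D14, D21 and D28.
- SAE rule: even if discharge on day *d* counted as completing the study, reporting would run to *d* + 30, which is later than 28 for any *d* ≥ 0. However, the rule works from the investigator becoming aware of an event and schedules no contact.

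So for day 28 the sections contradict each other, but the information can be obtained.

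**4. If 7.4 is applied as discharge-first, could the arms be observed for different lengths of time?** The Protocol gives no discharge proportion. As an assumption, take the primary event (two-point improvement or discharge) as a proxy for discharge.

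- Section 9.2.1 proportions: 0.50 × 260 = 130 control and 0.70 × 260 = 182 treated patients would leave follow-up.
- Section 9.2.1 medians, exponential times: rate λ = ln 2 / median, proportion leaving by day 28 = 1 − exp(−28λ), mean observed days = that proportion / λ.
  - Control, median 11: λ = 0.0630, proportion 83%, mean 13.2 of 28 days.
  - Treated, median 7.7: λ = 0.0900, proportion 92%, mean 10.2 of 28 days.

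The proxy overstates discharge wherever patients improve by two points and stay in hospital. With no treatment effect on discharge timing, the two arms have the same distribution of observed time and no imbalance arises.

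**5. Does the fix affect the sample size?** First reproduce the plan's figure. Schoenfeld's formula with hazard ratio 0.7, one-sided 0.025 and 85% power gives 4 × (1.960 + 1.036)² / (ln 0.7)² = 282.3, so 283 events. Dividing by the mean event proportion (0.50 + 0.70)/2 = 0.60 gives 472, as stated in section 9.2.2, and 472 × 1.1 gives the stated 520. Mortality does not enter, so these numbers do not change.

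**The case against.** The best defence is that the Protocol, read as a whole, intends follow-up to day 28 for everyone. The flow chart makes no exception for discharge. Two scale categories would be pointless without post-discharge assessment. The swab schedule in 7.4 itself runs to day 28 with a stopping rule based on negative tests rather than discharge. Section 9.4 censors the primary endpoint at day 28, or at last contact for those lost earlier. The SAE window runs past day 28 for every patient. On this reading 7.4 is loosely worded, and the six months to last patient last visit suggest that a day-90 check was intended and left out of Table 4.

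Much of this stands. A reader might infer that 28-day mortality cannot be measured either. The documents do not support that: the flow chart and the SAE rule both reach day 28. A reader might also infer that discharged patients are bound to be lost at different times in the two arms. That needs the discharge-first reading of 7.4, sites that set aside the flow chart, and a real effect on discharge timing, so it is a conditional risk and not a property of the plan. Nor do the 50% and 70% figures show how many patients would lack day-28 status, because they describe a composite and not discharge.

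The defence does not reach day 90. Spare calendar time is not a procedure, and even the most generous reading of every window ends at day 58. Nor does it settle day 28 at site level, because the absence of an SAE report does not show that a discharged patient is alive, and section 7.4 is the place where a site looks up how long to follow.

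**Conclusion.** The point holds for day 90 without further assumptions. The endpoint is named, nothing ascertains it, and at least 32 days are uncovered for every patient. Day-90 status will be missing for all patients not already known to have died, unless sites act outside the Protocol.

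For day 28 the finding is an internal contradiction between section 7.4 and the flow chart. If sites stop at discharge, the post-discharge ordinal scores and an actively confirmed vital status are lost. If treatment also shortens time to discharge, the loss is unequal. On the proxy and exponential assumptions above, mean observed time would be about 13.2 days in control against 10.2 in the treated arm. Deaths after discharge would then be missed more often in the arm discharged earlier. The number missed cannot be estimated, because the Protocol gives no post-discharge death rate.

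The primary endpoint is not harmed: live discharge is itself an event, so ending follow-up there censors nobody. The matter should be corrected, but it does not threaten the primary analysis.

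**What to change.** - Amend section 7.4 so that all randomised patients are followed to day 28 regardless of discharge, with the ordinal category and vital status obtained by telephone or record check after discharge. This brings it into line with the flow chart.
- Add a day-90 vital-status check to Table 4 for both arms. If day 90 is not wanted, delete 90-day mortality from section 2.4 and the Summary.

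The cost is one or a few calls or record checks per patient, with no extra visit and no change to the 472 or 520 patients. The planned timeline already allows for day 90. Deleting the endpoint costs nothing operationally but gives up the only planned longer-term outcome. The change is best made early, since post-discharge status not collected at the time may not be recoverable at database lock.

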#### 1.5.1. Research hypothesis

We assume superiority of combination therapy compared to standard of care.

Time to discharge or clinical improvement by 2 points in the standard of care arm is expected to be (median: 11 days). The exact treatment effect from Favipiravir tablets + Hydroxychloroquine is not exactly known but can be approximated using prior clinical studies. A study comparing the effect of Favipiravir to lopinavir/ritonavir on virus clearance has shown a 64% reduction in time to viral clearance in the Favipiravir arm. This was equivalent to a median of 11 days. We assume that clinical improvement might take place a little later to viral clearance and therefore we assume that the treatment arm might result in a minimum clinically meaningful expected reduction of 30% (from a median of 11 days to a median of 7.7 days). This is equivalent to a Hazard ratio of 0.7.

We further assume, that 50% of the patients in the control group will have clinical improvement/ discharged and 70% will have clinical improvement/discharged in the treatment arm.

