### 9.2 Sample Size and Power Considerations

#### 9.2.1 Assumptions and Study Hypothesis:

- a. **Time to discharge or clinical improvement by 2 points** in the standard of care arm is expected to be (median: 11 days; Cai Q, Y.M., Liu D, Chen J, Shu D, Xia J, , Experimental Treatment with Favipiravir for COVID-19: An Open-Label Control Study. 2020.).
- b. The exact treatment effect from Favipiravir tables + Hydroxchloroquine is not exactly known but can be approximated using prior clinical studies. A study comparing the effect of Favipiravir to lopinavir/ritonavir on virus clearance has shown a 64% reduction in time to viral clearance in the Favipiravir arm. This was equivalent to a median of 11 days. We assume that clinical improvement might take place a little later to viral clearance and therefore we assume that the treatment arm might result in a minimum clinically meaningful expected reduction of 30% (Median 7.7 days). This is equivalent to a Hazard ratio of 0.7.

- c. We further assume, that 50% of the patients in the control group will have clinical improvement/ discharged and 70% will have clinical improvement/discharged in the treatment arm
- d. It is anticipated that very few of these subjects will be randomized and not start study treatment (and so be excluded from the primary analysis) or be lost to follow-up (and so have missing data for the primary endpoint). Given certain uncertainties however, we have included a nominal 10% drop out rate.
- e. The primary hypothesis of the current study is  $H_0: HR = 1$  vs.  $H_1: HR \neq 1$  ; and HR is the hazard ratio of treatment compared to control arm.

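### PCR swabs appear to stop at discharge, which the plan expects sooner on treatment, so the crude negative-conversion rate can be attenuated or reversed against a drug that speeds discharge

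*Protocol*

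**What the plan says.** Section 2.4, item 4, makes "PCR test negative conversion rate and days from positive to negative" a secondary endpoint, and section 2.2 makes the duration of viral shedding a secondary objective.

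Section 7.4 opens with "The follow up period would be till discharge from the hospital or day 28 from randomization" and then places the serial swabs within that period: day 1, then days 5 ± 1, 10 ± 2, 14 ± 2, 21 ± 2 and 28 ± 3, "or until 2 consecutive testing are negative which comes first". It adds "Any extra Respiratory PCR COVID19 samples requested by the treating team will be recorded". It names no swab at discharge and no swab after it, and it does not say how a patient who leaves still positive is counted.

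The row "Covid-19 PCR from Respiratory sample" in the flow chart (section 8) is marked at D0, D1, D5, D10, D14, D21 and D28, with no discharge limit.

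Section 2.3 includes live discharge in the primary event. Section 1.5.1 expects the time to that event to fall "from a median of 11 days to a median of 7.7 days" on treatment.

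**The concern.** If swabs end when the patient goes home, the benefit the trial hopes to show removes treated patients from PCR sampling earlier than controls. On scheduled swabs alone, two consecutive post-baseline negatives cannot be seen before the day-10 visit. A patient discharged earlier, or discharged while still positive, has no later result.

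Neither simple way of handling such patients is neutral. Counting them as not converted penalises the arm with faster discharge. Dropping them keeps the patients who stay longest, and does so unequally by arm. The virology comparison would then partly measure length of stay. An analysis plan can change how these patients are handled, but it cannot supply swabs that were never taken.

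**Working it through.** The protocol gives no figure for missed swabs, so the check uses its planning inputs.

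**Inputs.**
- Medians of 11 and 7.7 days for discharge or a two-point improvement (sections 1.5.1 and 9.2.1). The stated 30% reduction reproduces: 11 × 0.7 = 7.7.
- Event proportions of 50% and 70% (section 9.2.1).
- Swab days 5, 10, 14, 21 and 28 (section 7.4).
- Viral clearance medians of 11 days on the comparator and 4 on favipiravir, from the study cited in section 1.5.5.2.

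**Assumptions not in the protocol.** Exponential times, clearance independent of discharge, a cleared patient stays negative, and swabs only while in hospital.

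**Step 1: share with the primary event before a swab.** F(t) = 1 − 2^(−t/median).

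| Day | Control (11) | Treated (7.7) |
|---|---|---|
| 5 | 27.0% | 36.2% |
| 8 (early edge of the day-10 window) | 39.6% | 51.3% |
| 10 | 46.7% | 59.4% |

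These shares are for the composite event. From baseline category 3 or 4, a two-point gain means leaving hospital. A gain from 5 to 3, or from 6 to 4, does not. The day-10 values are therefore upper bounds on discharge under this curve. If half of the events are discharges they become 23% and 30%.

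The medians imply 83% and 92% with the event by day 28, well above 50% and 70%. Reading those proportions at day 28 instead gives 1 − 0.5^(10/28) = 21.9% and 1 − 0.3^(10/28) = 34.9% by day 10. The gap between arms is about 13 points on either basis, and about 6 points if half of the events are discharges.

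**Step 2: observed conversion, with unsampled patients counted as not converted.** Take discharge medians of 11 and 7.7, so that every event is a discharge. Let p_k be the probability of clearing between swab k−1 and swab k, and S_k the probability of still being in hospital at swab k. Then
- one negative = Σ p_k S_k
- two consecutive negatives = Σ p_k S_(k+1)

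For clearance median 11, p = 0.270, 0.197, 0.119, 0.148, 0.095. S is 0.730, 0.532, 0.414, 0.266, 0.171 for control and 0.638, 0.407, 0.284, 0.151, 0.080 for treated.

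One negative, control: 0.270×0.730 + 0.197×0.532 + 0.119×0.414 + 0.148×0.266 + 0.095×0.171 = 0.407. The other cells follow in the same way.

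| Clearance median, control v treated | One negative | Two negatives |
|---|---|---|
| 11 v 11 | 40.7% v 31.6% | 28.2% v 19.6% |
| 11 v 7.7 | 40.7% v 38.6% | 28.2% v 24.2% |
| 11 v 4 | 40.7% v 50.5% | 28.2% v 32.3% |

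With no viral effect, the treated arm looks worse by about 9 points. With a 30% shorter clearance median it still looks slightly worse. With the cited medians it looks better. For that last row, full sampling to day 28 would show two negatives in 1 − 2^(−21/11) = 73% v 1 − 2^(−21/4) = 97%, a 24-point difference, against the 4 points observed here.

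**Step 3: leave unsampled patients out.** Dividing the one-negative rate by the share reaching day 5, equal clearance gives 0.407/0.730 = 56% v 0.316/0.638 = 50%. With a treated clearance median of 7.7 it gives 56% v 60%, so the sign now favours treatment. The answer depends on the handling rule.

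**Step 4: does a discharge swab alone cure the crude rate?** If status is known up to discharge or day 28, the observed rate is a/(a+b) × (1 − 2^(−28(a+b))), where a and b are the reciprocals of the clearance and discharge medians. Equal clearance gives 0.500 × 0.971 = 49% v 0.412 × 0.986 = 41%. The bias in the crude rate remains.

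**The case against.** The best reply is that the protocol never says outright that swabbing stops at discharge. Section 7.4 does not say which of discharge and day 28 governs, the swab sentence has its own stopping rule, the flow chart runs PCR to D28, and 90-day mortality implies some later contact. The footnotes attached to this endpoint and to the PCR row are not in the text available. This stands: the end at discharge is the natural reading, not an explicit one. It is also why the two passages need reconciling, since each reading requires an edit.

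A reader might infer that 47% and 59% of patients go home before day 10. The documents do not support that, because the medians describe discharge or a two-point improvement. The early part of the exponential curve is also doubtful, since section 4.2 excludes discharge within 72 hours.

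A reader might also infer that the endpoint cannot be scored. That is too strong. On the Step 1 model 73% and 64% of patients reach the day-5 swab, extra clinical swabs are recorded, and two consecutive negatives is a rule for stopping swabs, which section 2.4 does not make the definition of conversion. Extra swabs, however, depend on the treating team and are not guaranteed before discharge.

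Finally, section 9.4 allows for censoring in quantitative secondary variables, and the rest may sit in an analysis plan not shown. That partly covers days to negative. It does not cover the crude rate, and it cannot supply missing swabs.

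**Conclusion.** The point holds as a risk of differential loss of PCR data. Section 7.4 and the flow chart leave open whether swabs continue after discharge. If they do not, the crude conversion rate is biased against whichever arm discharges sooner.

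Up to 47% v 59% could miss the day-10 swab, or about 22% v 35% on the other reading of the plan's inputs. Under equal 11-day clearance, with unsampled patients counted as not converted, the observed rates are 41% v 32% for one negative and 28% v 20% for two.

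It does not follow that an effective drug must show a lower conversion rate. With the cited 11- v 4-day clearance medians the treated arm stays ahead, and the effect is attenuated, not reversed. Reversal needs a small viral effect and a rule that counts unsampled patients as not converted, or no viral effect at all under the exclusion rule in Step 3.

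The sizes rest on exponential times, on independence of clearance and discharge, and, except where stated, on every primary event being a discharge. The endpoint is secondary, and the primary analysis is unaffected.

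**What to change.** 1. Reconcile section 7.4 with the flow chart by stating whether scheduled swabs continue after discharge.
2. If they do not, amend section 7.4 so that the next due swab is brought forward to the day of discharge for any patient not yet confirmed negative.
3. In section 2.4, define the endpoint as time from randomisation to first negative PCR, analysed as time-to-event, with patients discharged still positive censored at their last swab.
4. Because that censoring may be informative, add a bounding analysis that treats all such patients as converted and then none. Do not base the comparison on crude conversion rates.

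Items 2 and 3 are both needed, since Step 4 shows that the discharge swab alone leaves the crude rate biased.

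The cost is at most one already scheduled swab moved earlier per patient, and somewhat wider intervals. Some discharge days, such as day 7, fall outside the current windows (4–6 and 8–12), so the window wording must allow the move. Sample size and the primary analysis do not change.
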